### Allocation

Patients who are eligible to participate in the study will be allocated to either the creatine and exercise group or the exercise alone control group (1:1). Randomization will be performed through the study’s REDCap (Research Electronic Data Capture; Vanderbilt University) database. We will use randomized blocks to conceal the group allocation results from the patients, recruitment staff, and assessment staff, and concealment will be maintained until the patients complete the baseline assessments. The research pharmacy at the Mays Cancer Center will conceal the randomization and will direct the research team to assign study participants to specific groups. A sample of 15 breast cancer survivors will be enrolled in each group with the goal of having 12 completers in each group. Due to the nature of the study, the principal investigator and study participants will not be blinded. However, to alleviate any issues with assessment fidelity, the research assistant who will be performing the outcome assessments will not be aware of the groups to which participants are randomized. Further, the statistician who will be supporting the analyses in the study will be blinded as well.

### Exercise Intervention

All participants will engage in 3 center-based exercise sessions each week for 12 weeks. Each session will last roughly 1 hour and include a 10-minute warm-up and a 50-minute stimulus phase. Exercise sessions will be held on nonconsecutive days to allow for adequate rest and recovery. The prescription will include 2 or 3 sets of 6 exercises, which will be performed at a 10-repetition maximum intensity (ie, participants will be able to perform only 8 to 12 repetitions per set), as per the American College of Sports Medicine’s guidelines for exercise testing and prescription [29] and the consensus statement on exercise guidelines for cancer survivors [30]. Each session will consist of the following exercises, which will be done in the following order: chest press, leg press, seated row, shoulder press, leg extension, and leg curl. The resistance load will be set at 70% of the measured or estimated 1-repetition maximum. If participants cannot perform an exercise with this resistance load, the load will be reduced to allow them to complete the prescribed repetitions for each set. Participants will complete 2 sets of each exercise in week 1. This will allow participants to familiarize themselves with the resistance load and will minimize the risk of injury for novice participants. Starting in week 2, participants will transition to performing 3 sets of each exercise. The load will be increased when a participant is able to perform 12 repetitions in 2 of 3 sets for an exercise. Participants’ heart rates will be monitored continuously during exercise sessions. Self-reported perceived exertion will also be recorded periodically during exercise sessions [31], and this information will be used to track the subjective experiences of participants and interpret adherence data.

### Creatine Dosing Protocol

Participants who are randomized to receive creatine (experimental group) will be initially dosed at 20 g per day for 7 days to boost the availability of creatine systemically [32]. Thereafter, the dose will be reduced to 5 g per day for maintenance throughout the duration of the 12-week protocol. This dosing protocol is based on the traditional dosing protocol for healthy individuals, which includes a loading phase (5 g of creatine taken 4 times per day) that is followed by a low-dose maintenance period (5 g of creatine per day) for maintaining creatine stores [12]. The individuals in this group will receive creatine in powder form at 4 different schedules based on their progress throughout the protocol. Each bottle of creatine will contain a 5-mg dosing spoon. Bottle 1 will be provided at the start of the study, and an equivalent dose for the loading phase will be assigned in week 1 of the study. In week 2, participants will return to the clinic and be provided with 21 days’ worth of creatine doses (5 g/day). At weeks 5 and 9, participants will again return to the clinic and be given 28 days’ worth of creatine doses (5 g/day). Bottles will be exchanged at these scheduled intervals, and dosing adherence will be determined by measuring the amount of creatine that remains in the bottles. For weeks 2 to 12, participants will also be asked to take the creatine at approximately the same time of the day and enter the time of dosing in a dosing diary. The individuals in this group will have safety labs drawn after the loading phase to ensure normal kidney function, and electrocardiography will be performed to rule out any abnormalities. Participants will be removed from the creatine group if the lab results show serum creatinine levels of >2 times the upper limit of normal or estimated glomerular filtration rates of <30 mL/min/1.73 m^2^. These participants will complete the remaining exercise interventions.

### Study Procedures

#### Telephone Screening

Potential participants will undergo telephone screening to rule out clear, excluding medical conditions prior to in-person screening. Individuals who are known to meet no clear exclusionary criteria will be invited to an initial screening visit.

#### Screening Visit

At the screening visit, participants will read and sign the informed consent form. Once consent is provided, a complete medical history and physical exam will be performed to ensure that the participants meet the inclusion criteria for the study. This will include measurements of vital signs, height, and body weight. Blood will be collected following an overnight fast for clinical lab tests, which will include renal function testing, comprehensive metabolic panels, and lipid and complete blood count tests. Resting electrocardiograms will be acquired and evaluated by a clinician to confirm a healthy heart rate and rhythm. Questions regarding the intent to become pregnant will be asked. A mood disorder questionnaire will be completed by participants and evaluated by study staff to assess for bipolar mood disorder. Subjects who meet the study eligibility criteria will be scheduled for study assessments.

#### Outcome Assessments

Assessments will be performed at baseline and at the end of the study (Table 2).

**Table 2 table2:** Study assessments and methods.

Assessment	Method
Renal function testing, metabolic panels, and lipid and complete blood count tests	Lab test
Muscle strength (power and torque)	Dynamometry
Muscle strength	1-repetition maximum and 10-repetition maximum training
Body composition and bone density	Dual x-ray absorptiometry
Muscle cross-sectional area	Magnetic resonance imaging
Muscle creatine, phosphocreatine, and adenosine triphosphate	Magnetic resonance spectroscopy
Physical function	6-minute walk test
Quality of life	European Organization for Research and Treatment of Cancer Quality of Life Questionnaire-C30 and European Organization for Research and Treatment of Cancer Quality of Life Questionnaire-BR23

#### Body Composition

Body composition (fat mass, muscle mass, and bone) will be measured via dual x-ray absorptiometry. By using dual x-ray absorptiometry scans, we will measure whole-body and regional adipose and lean mass [33] as well as bone mineral density.

#### Strength and Physical Function

A 1-repetition maximum test will be performed to evaluate the maximum amount of force that can be generated through a full range of motion for a particular body region [34]. This will be directly tested for chest presses and leg presses and estimated (via 10-repetition maximum testing) for shoulder presses, leg extensions, and leg curls. Isometric knee extensor strength will be assessed in the right leg of each participant (unless contraindicated) by using a Biodex dynamometer (Biodex Medical Systems). The isometric maximum voluntary contraction force will be measured at approximately 60° knee flexion [35]. The average values from 3 attempts and percent variance will be recorded. Dominant isometric handgrip strength will also be tested by using a handgrip dynamometer (Jamar Plus+ Digital Hand Dynamometer; Jamar Plus+) [36]. Participants’ 6-minute walk distances will be assessed to measure endurance function by using a standardized protocol [37].

#### Patient-Reported Outcomes

Study participants will complete the European Organization for Research and Treatment of Cancer Quality of Life Questionnaire (EORTC QLQ)-C30 (version 3) quality of life survey and EORTC QLQ-BR23 survey for breast cancer survivors [38,39]. The EORTC QLQ-C30 is a 30-item measure of health-related quality of life. It includes 6 functional scales (physical, role, emotional, social, cognitive, and global quality of life scales), 3 symptom scales (fatigue, pain, and nausea and vomiting scales), and 6 single items (dyspnea, sleep disturbance, appetite, diarrhea, constipation, and financial difficulties). The EORTC-QLQ-BR23 is a 23-item measure of the symptoms and problems experienced by breast cancer survivors.

#### Muscle Cross-sectional Area and In Vivo Assessments

Magnetic resonance imaging will be used to measure the right midthigh muscle cross-sectional area (unless contraindicated) by using a whole body 3.0 T magnetic resonance imaging scanner (TIM Trio; Siemens AG). At the same time, intramuscular creatine, phosphocreatine, and ATP content will be assessed in vivo by conducting magnetic resonance spectroscopy (MRS), as previously described [40,41]. A phosphorus-31/hydrogen-1 dual-tuned, rigid, arc-shaped surface coil (RAPID Biomedical GmbH) will be positioned under the vastus lateralis. The vastus lateralis muscle was chosen for in vivo analysis because of the superficial positioning of the muscle and because it is the largest muscle in the quadriceps muscle group, which is the largest and strongest muscle group in the body. Lower extremity muscle weakness is also associated with long-term fatigue in breast cancer survivors [3]; thus, in vivo measurements are warranted for this muscle. An external reference 6-mL plastic vial with an 850mM concentration of methylenediphosphonic acid will be fixed to the center of the coil. Methylenediphosphonic acid was chosen due to its resonance frequency of around 22 parts per million downfield from phosphocreatine; this does not overlap with any relevant metabolite peaks. After a subject is scanned, a 15-cm–diameter, 4-L, plastic, cylindrical leg phantom containing 35mM phosphoric acid will be placed on the coil and scanned by using the same MRS parameters and slab positions, so that the data can be collected from the same area within the radio frequency excitation field of the coil. A slice-selective phosphorus-31 MRS slab sequence (excitation pulse repetition time=10 seconds; time to echo=2.3 seconds; number of signals averaged=16; slice thickness=25 mm; receiver bandwidth=3000 Hz) will be performed for the quadriceps muscles of subjects and for the previously described leg phantom. Raw spectral data will be analyzed with Java Magnetic Resonance User Interface software [42], and the processing steps will include apodization to 5 Hz and Fourier transformation and phase correction. For spectrum quantification, the AMARES (Advanced Method for Accurate, Robust, and Efficient Spectral Fitting) algorithm [43] will be used.

### Capturing and Monitoring Adherence

Adherence to creatine supplementation will be assessed by measuring the quantity of creatine that is left in the returned bottles, as described in the *Creatine Dosing Protocol* section. Individuals will not be withdrawn from the study for noncompliance with the creatine dosing regimen. The dosing quantity (number of scoops) and the dosing time will be documented in a dosing diary. Each exercise session will be documented, and information regarding session duration time as well as exercise mode and intensity during each training session will be documented. Participants will be encouraged to adhere to the protocol to the best of their ability. Participants will be withdrawn if more than 33% (12/36) of exercise sessions are missed.

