**Figure 1 figure1:**
[figure not shown]
Individuals randomized to the creatine group will exercise 3 times per week for 12 weeks and take creatine in powder form as indicated. Individuals in the control group will exercise 3 times per week for 12 weeks without creatine dosing.

**Table 1 table1:** Study schedule of events.

Event	Screen day (−28 to −7 days)	Baseline assessments (−7 to −2 days)			Study week				12-week end-of-study assessments (>2 days and <7 days after the last exercise session)	
		Visit A	Visit B	Week 2		Week 5	Week 9	Visit A		Visit B
Phone screen	✓									
Physical exam	✓							✓		
Medical history	✓			✓		✓	✓	✓		
Medication history	✓			✓		✓	✓	✓		
Clinical labs	✓			✓				✓		
Electrocardiography	✓			✓						✓
Vital signs	✓							✓		
Height	✓									
Weight	✓							✓		
Body circumference	✓							✓		
Waist to hip ratio	✓							✓		
Mood disorder questionnaire										
Pregnancy test		✓						✓		
Handgrip dynamometry		✓						✓		
Isometric leg strength		✓						✓		
Dual x-ray absorptiometry		✓						✓		
6-minute walk test		✓						✓		
Survey completion		✓						✓		
Magnetic resonance imaging and magnetic resonance spectroscopy			✓							✓
1-repetition and 10-repetition maximum testing			✓							✓
Exercise familiarization			✓							
Dispense creatine (20 g/day)			✓							
Dispense Creatine (5 g/day)				✓		✓	✓			

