### Statistical Analysis

The proposed analysis of 30 participants is based on a feasibility assessment [45]. Based on a preponderance of published feasibility and pilot studies, a minimum sample size of 15 participants per group was chosen to complete the study and estimate parameters for future studies [46,47].

Data on recruitment, adherence, and attrition rates will also be collected. Participants that withdraw from the study or are withdrawn for safety reasons will not be replaced.

Statistical analyses will be performed by using IBM SPSS 19.0 software (IBM Corporation). Descriptive statistics will be used to summarize the data. The primary analysis will be an intent-to-treat analysis, which will be conducted by using a 2-sided, stratified log-rank test. Cox proportional hazard regression models will be used to estimate hazard ratios with 95% CIs to quantify the effect of the intervention after adjusting for stratification, age, and BMI. We will also conduct secondary analyses for nonadherence, the rate of perceived exertion, and the number of exercise sessions completed. Pearson product moment correlation analyses will be used to measure associations among biomarkers of body composition, physical function, and quality of life measures. A *P* value of <.05 will be considered statistically significant, and all statistical tests will be 2-tailed. The results of our study will be used to calculate power and determine sample sizes for future research in this field.

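### The attendance rule appears to withdraw poor attenders from the study before the only post-baseline outcome visit, which conflicts with the declared intent-to-treat analysis

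*Protocol article*

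**What the plan says.** Under Capturing and Monitoring Adherence, the protocol article states: "Participants will be withdrawn if more than 33% (12/36) of exercise sessions are missed". Just before that, it treats the supplement differently: "Individuals will not be withdrawn from the study for noncompliance with the creatine dosing regimen". The Creatine Dosing Protocol section also keeps participants in the exercise programme when creatine is stopped on laboratory grounds.

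The denominator of 36 comes from the Exercise Intervention section: "All participants will engage in 3 center-based exercise sessions each week for 12 weeks".

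On outcome timing, the Outcome Assessments section says: "Assessments will be performed at baseline and at the end of the study (Table 2". Table 1 places the final visit under the column heading "12-week end-of-study assessments (>2 days and <7 days after the last exercise session".

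Under Statistical Analysis: "The primary analysis will be an intent-to-treat analysis". The Allocation section adds: "A sample of 15 breast cancer survivors will be enrolled in each group with the goal of having 12 completers in each group". It also states that participants and the principal investigator are not blinded.

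**The concern.** Intent-to-treat analysis needs outcomes from everyone randomized, whatever they did afterwards. Attendance is something participants do after randomization. Here they know which arm they are in, so attendance, and the reasons for missing sessions, can differ between arms. A rule that removes people for poor attendance, placed before the only follow-up measurement, makes the protocol itself a source of missing outcomes. The comparison of strength, body composition and walking distance would then rest on those who attended well enough to stay.

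An analysis plan can choose how to handle missing values, but it cannot recover measurements that were not made. The article says the results will be used to calculate power and sample sizes for later research, so a distorted estimate would carry into the next trial.

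**Working it through.** **1. The plan's own figures.** 3 sessions × 12 weeks = 36 sessions, and 12/36 = 33.3%. Both reproduce.

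**2. What withdrawal means.** The creatine sentence says noncompliance does not lead to withdrawal from the study. The attendance sentence, in the same paragraph, says participants will be withdrawn and adds no qualifier. The natural reading is that missed exercise leads to what missed creatine does not. Where creatine is stopped for laboratory results, the article says what happens next; for poor attenders it says nothing.

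**3. What withdrawal costs.** The efficacy outcomes in Table 2 are scheduled at baseline and end of study only. Table 1 shows no interim strength, DXA, walk, MRI or questionnaire measurement. A participant who leaves in between has no post-baseline outcome.

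**4. The visit window for someone who stops early.** Take a participant who attends every session and then stops outright.
- More than 12 missed means at least 13 missed, so at most 36 − 13 = 23 attended.
- 23 sessions at 3 per week end in week 8 (23/3 = 7.7).
- If the last session means the last one attended, a window closing within 7 days ends by about week 9, some three weeks before week 12.
- Missing 13 sessions at 3 per week takes over four weeks (13/3 = 4.3), so that window has passed before the threshold is crossed.

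The window therefore gives no usable 12-week visit for such a person, although it does not itself exclude anyone.

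**5. Illustrative bias.** Let p be the proportion withdrawn in an arm and g the mean outcome gap, retained minus withdrawn, in SD units. The full-arm mean is (1 − p) × retained mean + p × withdrawn mean, so the retained mean exceeds the full-arm mean by p × g. With the same g in both arms:

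shift in the group difference = (p in one arm − p in the other) × g

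The splits and gaps below are assumptions; the article gives none.

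| Withdrawn (of 15 per arm) | g = 0.5 SD | g = 1.0 SD |
|---|---|---|
| 3 vs 3 | 0 | 0 |
| 4 vs 2 | 2/15 × 0.5 = 0.07 | 2/15 × 1.0 = 0.13 |
| 5 vs 1 | 4/15 × 0.5 = 0.13 | 4/15 × 1.0 = 0.27 |

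If withdrawn participants do worse, the shift favours whichever arm loses more of them. Equal numbers protect only if the gaps are also equal: with 3 of 15 withdrawn in each arm and gaps of 1.0 and 0.5 SD, the shift is 3/15 × 0.5 = 0.10 SD.

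**The case against.** The strongest objection is that the article nowhere says poor attenders miss the final assessment or leave the analysis set. Off-intervention follow-up and analysis populations are details that a condensed article may leave to the full protocol or SAP. This stands as a limit on certainty: a reader might infer that these outcomes are definitely never collected, and the text supports only that they probably are not. It does not remove the point, because the rule is stated and, read in context, it conflicts with the declared analysis.

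Differential withdrawal is also unproven. The rule and the exercise programme are the same in both arms, the article cites adverse effects in only 2 of 333 patients taking creatine in earlier cancer studies, and it reports none in the creatine arm so far. That is why no direction is claimed. Moreover, with 12 per arm the standard error of a difference is √(2/12) = 0.41 SD, so even 0.27 SD is less than one standard error. The sample size is justified on feasibility grounds. Both facts limit the practical weight of the bias, but neither is a reason to give up measurements that could be made.

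Four further readings are tempting and not supported:
- **That timing the visit from the last session removes participants.** It bars no one by itself. The column is labelled as a 12-week assessment and the window may be meant mainly as a rest interval. The difficulty is confined to people who stop early.
- **That the rule costs 3 of 15 per arm, widening confidence intervals by about 12%** (√(15/12) = 1.118). The 12-completer goal covers attrition from all causes, and the article attributes none of it to this rule.
- **That the rule inflates reported adherence.** Each session is documented, adherence and attrition rates are collected, and secondary analyses of nonadherence and sessions completed are planned.
- **That the threshold contradicts itself.** Exactly 12 missed is 33.3%, above 33% but not above 12/36. This is rounding, and an editorial matter only.

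**Conclusion.** The concern holds as a conflict between a stated withdrawal rule and a stated analysis principle. Followed as written, the rule would probably make the protocol itself lose outcomes of randomized participants on account of attendance after randomization. The planned nonadherence analyses do not repair this, because the poorest attenders would have no end-of-study outcome to analyse.

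The size and direction of any bias are unknown. The range of 0.07 to 0.27 SD depends wholly on the assumed unequal withdrawal (4 vs 2 to 5 vs 1 of 15) and the assumed gap of 0.5 to 1 SD. It is zero when withdrawal and gaps are equal across arms. The conclusion also rests on reading withdrawal as withdrawal from the study, and on there being no follow-up provision in a document not shown.

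**What to change.** Reconcile the adherence section, Table 1 and the Statistical Analysis section by separating two events: stopping the exercise programme and leaving outcome follow-up.

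- State that participants who cross the attendance threshold are still invited to the end-of-study assessments and are analysed in the group to which they were randomized. Full withdrawal from follow-up would then be the participant's own choice.
- For participants who stop exercising early, time the end-of-study visit at 12 weeks from the start of the intervention. The Table 1 window can stay for those who finish the programme.
- Keep low attendance as an adherence outcome, and use the threshold to define a per-protocol set for sensitivity analysis.
- As an editorial tidy-up, state the threshold once as a session count.

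This leaves the threshold and the exercise programme unchanged. The cost is a short amendment and a few extra visits for people already among the 30. Some will decline, so having all 15 per arm assessed is a ceiling. With 9 enrolled as of October 2021, 30 − 9 = 21 planned participants were still to come at that date and could be covered from enrolment.

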### Monitoring Adverse Events

Adverse events will be assessed during each interaction with a participant (ie, 3 times per week). Before and after each exercise session, participants will be asked about how they are feeling. If the answer is anything other than “feeling fine,” the participant will be queried about the date and time of the onset of an adverse event, self-perceived severity, and any self-administered treatments. Upon the conclusion of the intervention, each adverse event will be graded by medical professionals based on severity, the event’s relationship to the study intervention, the actions taken by the study personnel and participants, adverse event outcomes, whether the event was expected, and whether the event was serious. We will use the Common Terminology Criteria for Adverse Events version 5.0 [44] to grade the adverse events.

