### Safety and Toxicity of Creatine

Creatine has not been evaluated by the Food and Drug Administration for safety; however, it is a widely used over-the-counter supplement. Creatine is one of the most highly studied supplements, and numerous studies have demonstrated its safety and tolerability [12,27]. In the four papers published to date on creatine supplementation in patients with cancer [22-25], only 2 of the 333 patients who were taking creatine reported any adverse effects (muscle cramping and mucus production) [22]. Other commonly identified side effects of creatine supplementation include nausea, diarrhea, dizziness, and gastrointestinal pain, but their severity is often mild [12,27].

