## Results

As of October 2021, a total of 19 patients have been screened, 12 have consented, and 9 have enrolled into the study. No adverse events have been reported in the creatine arm of the study. Muscle soreness and tingling associated with chemotherapy-related peripheral neuropathy have been reported as adverse events. No unexpected adverse events have been reported. Enrollment is planned to be completed by summer 2022.

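### The adverse event question asks how participants feel at exercise sessions, with no recall period or symptom list, so brief creatine side effects and illness during absence may be under-recorded or recorded late

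*Protocol article*

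**What the plan says.** The Monitoring Adverse Events section sets the frequency first: "Adverse events will be assessed during each interaction with a participant (ie, 3 times per week". It then gives the method: "Before and after each exercise session, participants will be asked about how they are feeling". An answer other than feeling fine opens the next step, in which "the participant will be queried about the date and time of the onset of an adverse event", along with self-perceived severity and any self-administered treatment. Nothing further is described for a participant who says she feels fine.

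The Exercise Intervention section fixes when the question can be asked: "All participants will engage in 3 center-based exercise sessions each week for 12 weeks", and "Exercise sessions will be held on nonconsecutive days to allow for adequate rest and recovery". Under Capturing and Monitoring Adherence, "Participants will be withdrawn if more than 33% (12/36) of exercise sessions are missed". That section also describes the dosing diary as a record of scoops and dosing time.

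The Safety and Toxicity of Creatine section names what to expect: "Other commonly identified side effects of creatine supplementation include nausea, diarrhea, dizziness, and gastrointestinal pain, but their severity is often mild". It also mentions muscle cramping among earlier cancer patients taking creatine.

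Table 1 repeats medical and medication history at weeks 2, 5 and 9 and at end of study, with laboratory tests and electrocardiography at week 2 and end of study. The Results section states: "No adverse events have been reported in the creatine arm of the study".

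**The concern.** Creatine is taken every day, but the question is put on three days a week and, as worded, concerns the participant's present state. Someone who had diarrhea the day after a session and has recovered by the next one can truthfully say she is fine, and the inquiry then stops. The onset question does not help her, because it comes after that gate: it dates events that are mentioned and does not draw out those that are not. A participant kept away by illness is not asked that day, and no inquiry tied to the missed session is described.

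The effects most easily lost this way are mild, passing complaints, and the article itself describes the expected creatine effects as often mild. The trial presents itself as the first to combine exercise with this dosing protocol in this setting, and its results are meant to inform later studies. Its tolerability statement will rest largely on this question.

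**Working it through.** **The plan's own figures.** 3 sessions × 12 weeks = 36 sessions, and 12/36 = 33.3%. Both agree with the article. A participant who misses 12 sessions still has 24, an average of 2 a week. At full attendance 3 of 7 days have a session and 4 of 7 (57%) do not. The same holds in the 7-day loading phase.

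**Share of symptoms still present at a session.** These assumptions are mine, not the article's: sessions on days 0, 2 and 4 of each week, onset equally likely at any time, one episode lasting D days, and an answer that reflects current state only. The gaps between sessions are then 2, 2 and 3 days. An episode is present at a session if it begins within D days before one, so

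capture(D) = [min(D,2) + min(D,2) + min(D,3)] / 7.

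- D = 1: (1 + 1 + 1)/7 = 3/7 = 43%
- D = 2: (2 + 2 + 2)/7 = 6/7 = 86%
- D = 3: (2 + 2 + 3)/7 = 7/7 = 100%

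If one session in three is missed, the remaining gaps are 2 and 5 days, 4 and 3 days, or 2 and 5 days, depending on which one is missed. Averaging the three cases:

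- D = 1: 2/7 = 29%
- D = 2: 4/7 = 57%
- D = 3: (5/7 + 6/7 + 5/7)/3 = 16/21 = 76%

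For a half-day symptom the figures are 1.5/7 = 21% and 1/7 = 14%.

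**Effect on seeing a symptom at all.** With 15 on creatine, true risk p and capture k, the chance of at least one recorded case is 1 − (1 − kp)^15.

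| Assumed true risk | Full capture | 43% capture |
|---|---|---|
| 5% | 54% | 28% |
| 10% | 79% | 48% |
| 20% | 97% | 74% |

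At a true risk of 10% and 86% capture (two-day symptoms), kp = 0.10 × 6/7 = 0.0857 and the chance is 1 − 0.9143^15 = 74%. This is close to the 79% under full capture.

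**What the reported zero can tell us.** Nine were enrolled. Assuming 4 or 5 of them on creatine (1:1; the split is not given) and a true risk of 10%, the chance of no recorded case is 0.9^5 to 0.9^4 = 59% to 66% under full capture. At 43% capture (kp = 0.0429) it is 0.957^5 to 0.957^4 = 80% to 84%. Zero is the likely result in either case.

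**Other routes, compared with the gap.**

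- Medical and medication history: real contacts, and the week 2 history comes straight after loading. From then on they are 3 to 4 weeks apart, and they are not described as adverse event queries.
- Laboratory tests and electrocardiography: they check kidney function and heart rhythm, not nausea, diarrhea or cramping.
- Dosing diary: scoops and time, with no symptom entry stated.
- EORTC QLQ-C30: it has nausea and diarrhea items, but is completed at baseline and end of study.

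**The case against.** The strongest reply is that a condensed description is being read as a verbatim script. Asking how someone feels may be a conversation in which she mentions yesterday's upset stomach. The follow-up on onset and self-treatment presupposes that events between sessions can be recorded. An absentee can report at her next session or history visit, which is delay and not loss. Recall windows, symptom forms and missed-visit procedures often sit in a full protocol that is not shown. The article calls the effects often mild but does not call them short-lived, and for symptoms of two or three days the loss at full attendance is small or nil.

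Much of this stands. A reader might infer that sessions are the only route to an adverse event record and that creatine effects are systematically missed. The documents do not support that: Table 1 provides histories at four later points, and participants may volunteer past symptoms. Nor do they show that only exercise complaints get through, since tingling linked to chemotherapy-related neuropathy was recorded.

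A reader might also infer a bias toward finding creatine harmless. The same question is put to both arms, so equal capture k would shrink a risk difference to k times its true size. But participants know their arm, and those on creatine may volunteer more. The net direction is not settled, and no between-arm safety test is among the stated objectives or analyses.

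What does not stand is that condensation explains everything. The article writes out the question, its timing, the gate and the follow-up fields. Applied as written, that rule lets resolved symptoms pass unasked.

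**Conclusion.** The point holds as a risk of under-recording or late recording, not as demonstrated loss. The stated rule is an open question at sessions, ended by an answer of feeling fine, with no recall period and no prompt for the effects the article itself expects. Its cost runs from none (three-day symptoms, full attendance) to more than half (one-day symptoms: 43% captured, or 29% if a third of sessions are missed). Those figures rest on assumed duration, random timing and answers limited to current state; any recall by the participant raises them. The scheduled histories provide partial back-up. The gap is widest for someone who stops attending, because no later adverse event contact is described for her.

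A reader might take the absence of events in the creatine arm as evidence of under-recording, or as evidence of tolerability. With 9 enrolled across both arms it is evidence of neither. The point merits a change because a clearly better question is available at little cost and, with 9 of 30 enrolled at the time of the article, most participants could still benefit.

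**What to change.** In Monitoring Adverse Events:

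1. Ask at each session about any new or worse symptom since the last contact. After a missed session, the question covers the whole missed interval.
2. Add a short fixed checklist of the effects named in Safety and Toxicity of Creatine (nausea, diarrhea, dizziness, gastrointestinal pain, muscle cramping), asked in the same words in both arms. Identical prompting matters because participants are not blinded.
3. State that the medical histories at weeks 2, 5, 9 and end of study are also adverse event queries covering the interval since the previous one.

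The cost is a reworded script and a short REDCap form, used by staff already present. The small downside is that more mild events will be recorded in both arms. Events collected before and after the change should be marked as such, since their counts will not be directly comparable.
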